## Abstract

**Background:**

Patients with cognitive impairments following a stroke are often denied access to inpatient rehabilitation. The few patients with cognitive impairment admitted to rehabilitation generally receive services based on outdated impairment-reduction models, rather than recommended function-based approaches. Both reduced access to rehabilitation and the knowledge-to-practice gap stem from a reported lack of skills and knowledge regarding cognitive rehabilitation on the part of inpatient rehabilitation team members. To address these issues, a multi-faceted knowledge translation (KT) initiative will be implemented and evaluated. It will be targeted specifically at the inter-professional application of the cognitive orientation to daily occupational performance (CO-OP). CO-OP training combined with KT support is called CO-OP KT. The long-term objective of CO-OP KT is to optimize functional outcomes for individuals with stroke and cognitive impairments. Three research questions are posed:Is the implementation of CO-OP KT associated with a change in the proportion of patients with cognitive impairment following a stroke accepted to inpatient rehabilitation?Is the implementation of CO-OP KT associated with a change in rehabilitation clinicians’ practice, knowledge, and self-efficacy related to implementing the CO-OP approach, immediately following and 1 year later?Is CO-OP KT associated with changes in activity, participation, and self-efficacy to perform daily activities in patients with cognitive impairment following stroke at discharge from inpatient rehabilitation and at 1-, 3-, and 6-month follow-ups?

**Methods/Design:**

Three interrelated studies will be conducted. Study 1 will be a quasi-experimental, interrupted time series design measuring monthly summaries of stroke unit level data. Study 2, which relates to changes in health care professional practice and self-efficacy, will be a single group pre-post evaluation design incorporating chart audits and a self-report survey. Study 3 will assess patient functional outcomes using a non-randomized design with historical controls. Assessments will occur during admission and discharge from rehabilitation and at 1, 3, and 6 months following discharge from rehabilitation.

**Discussion:**

This project will advance knowledge about the degree to which the implementation of a supported KT initiative can sustainably change health system, knowledge, and patient outcomes.

## Background

Patients with cognitive impairments following a stroke are often denied access to inpatient rehabilitation [1], despite evidence of its benefits for them [2]. These patients comprise up to 30 % of stroke patients [3]. In the instances when they are admitted to inpatient stroke rehabilitation, they generally receive services based on outdated impairment-reduction models, rather than recommended function-based approaches [4]. These two issues, reduced access to rehabilitation and the knowledge-to-practice gap, both stem from a reported lack of skills and knowledge on the part of stroke rehabilitation teams [4]. To address these issues, we will implement and evaluate a multi-faceted, supported, integrated knowledge translation (KT) initiative, targeted specifically at the inter-professional application of the cognitive orientation to daily occupational performance (CO-OP) approach [5]. The CO-OP approach is a contemporary, effective, cognitive strategy-based treatment approach aligned with Canadian stroke best practice recommendations for cognitive rehabilitation [6]. The long-term objective of this knowledge translation initiative is to optimize functional outcomes for individuals with cognitive impairments following a stroke. Three outputs are expected: (1) increased proportion of patients with cognitive impairments admitted to inpatient stroke rehabilitation; (2) enhanced capacity of inter-professional stroke rehabilitation team members to implement a cognitive-strategy based treatment approach; and (3) improved immediate and long-term functional outcomes for patients with cognitive impairments discharged from inpatient stroke rehabilitation.

This project is a collaboration between a group of knowledge users, lead by [name], and a group of researchers, lead by [name]. Lead knowledge user and decision maker, [name], is one of three regional directors within the Toronto Stroke Networks (TSNs), an organization charged with overseeing service delivery is in line with best practices and optimization of resources [7]. [name] has convened a knowledge user team of educators, a community re-engagement specialist, and management collaborators. To ensure an integrative KT strategy, these partners have been involved with every aspect of this project’s design, beginning with pre-project work to identify the problem and develop plans to address it.

The Toronto Stroke Networks developed a model to aid discharge from acute stroke care in a way that would maximize both patient outcomes and the efficient use of scarce rehabilitation resources, considering severity and patient characteristics [1]. The model indicates that 40 % of patients discharged from acute care should be transferred to specialized inpatient rehabilitation. However, in recent years, the actual proportion has ranged from 26 to 33 %, and the discrepancy comes in part from patients with cognitive impairment. Lack of access to inpatient rehabilitation may result in patients being transferred to assisted living facilities without the benefit of rehabilitation that could potentially have enabled them to return home. It may also contribute to the relatively poorer outcomes of patients with cognitive impairments, including higher rates of dependency and disability and lower mood and quality of life [8].

Ontario’s Ministry of Health and Long-Term Care and the TSNs have embedded access to inpatient rehabilitation for patients with cognitive impairment into care expectations [9]. However, inter-professional team members’ perceived lack of skills to support patients with cognitive impairment remains a major barrier to access to care. Interviews with professionals from Toronto-based rehabilitation teams revealed two important and related knowledge to practice gaps [4]. First, team members reported that they did not have the specialized knowledge and skills to work with stroke patients who were experiencing cognitive impairment. Second, when treating patients with cognitive impairments, team members reported using impairment-reduction models, considered to be outdated, rather than currently recommended function-based models that incorporate problem solving and strategy training. Contemporary function-based models are substantially better than pure impairment reduction models, in that they are associated with sustained improvements in everyday functioning, self-evaluation, and problem solving, among several other benefits [2]. Canadian Stroke Best Practice Recommendations state that interventions should be tailored to meet meaningful, functional patient goals [6]. The CO-OP approach aligns with these recommendations, and has demonstrated efficacy to improve function in people with stroke [10–12], including those with demonstrated cognitive impairment [12–14].

CO-OP, a functional, patient-goal-centered, problem-solving approach, is associated with improved function, activity performance, participation, and self-efficacy in people with stroke [10, 11, 13], and has demonstrated better efficacy than control conditions [12, 14, 15]. Table 1 provides an overview of relevant CO-OP stroke publications. CO-OP has seven key features that include client-chosen goals, dynamic performance analysis, cognitive strategy use, and guided discovery. In the first session, the patient and a rehabilitation clinician work together, using the Canadian occupational performance measure (COPM) [16], to select personally-valued activities which the patient needs or wants to do. These then form the basis of their rehabilitation goals and become the direct focus of the intervention. In the second session, the patient is taught a global cognitive strategy (Goal-Plan-Do-Check). This strategy is used in an iterative manner in all future sessions as the main problem-solving framework to facilitate skill acquisition/goal attainment. The patient identifies a goal, is guided by the clinician to discover a plan to achieve the goal, does the plan, and finally checks to see if the plan was implemented and if it worked to achieve the goal. Within the plan phase, the clinician uses guided discovery rather than explicit instruction to help the patient analyze the task to be performed and to discover individual strategies that are specific to the particular performance problems of that patient with that chosen activity. A detailed description of CO-OP’s theoretical foundations, key features, and administration procedures is available in a publication by Polatajko and Mandich, 2004 [5].

CO-OP has an established training infrastructure with available local trainers, and therefore is feasible and efficient to implement. However, given the multi-institutional environment, the need for shifts in attitudes and beliefs (the CO-OP approach requires therapists to give up a significant degree of control to the clients) and the relative ineffectiveness of passive KT strategies [17], CO-OP training by itself is unlikely to be sufficient to cause widespread, sustained practice change. Thus, we will implement a multi-faceted KT initiative that will combine institution-specific support, multi-sectoral collaboration, and managerial participation along with the established CO-OP training. These additional health system components are important in moving evidence to practice in complex environments, particularly when shifts in culture, attitudes, and behavior are required [18, 19]. Components of the project will integrate seamlessly with existing TSNs’ education and KT infrastructure, and will incorporate online components, including a virtual community of practice. These aspects will facilitate sustainability.

The knowledge to action framework developed by Graham et al. provides the foundation for this project [20]. The knowledge to action framework consists of a central knowledge creation cycle and a concurrent action cycle. Figure 1 depicts the knowledge to action framework with content specific to the CO-OP KT project. In preparatory work, issues were identified and knowledge was synthesized to develop strategies to mitigate those issues. The results led to development of the current project which begins with the phase of adapting the knowledge to the local context and identifying barriers to knowledge uptake, and will continue with selecting, tailoring, and implementing KT intervention, monitoring and sustaining knowledge use, and evaluating outcomes.

**Fig. 1 Fig1:**
[figure not shown]
Knowledge to action framework with CO-OP KT project content. Adapted from Graham et al. [20], the KTA framework consists of an inner knowledge creation cycle, depicted here as an *inverse triangle*; and a concurrent action cycle, depicted here as the *external circles. CO*-*OP* cognitive orientation to occupational performance, *IF* implementation facilitator, *TSNs* Toronto Stroke Networks, *VCoP* virtual community of practice, *ITS* interrupted time series, *KT* knowledge translation

Also informing the project are the inter-professional collaboration and inter-professional education constructs. Inter-professional collaboration incorporates effective working relationships among health care providers from different disciplines and their patients and enables optimal health outcomes by building on the foundational elements of “respect, trust, shared decision making, and partnerships” [21]. Inter-professional education emphasizes providers from multiple differences learning with, from, and about each other, and is interdependent with inter-professional collaboration.

Through this project, we expect to see improved knowledge and practice change in inter-professional stroke rehabilitation teams, manifested as greater implementation of cognitive rehabilitation best practices and greater self-efficacy to do so. Following directly from positive practice change, we also expect to see improvements at the health system and health outcome levels. Individual rehabilitation professionals and teams as a whole will come to see themselves as having the specialized knowledge and skills to facilitate functional improvement in patients with cognitive impairments. With this, the number of patients with cognitive impairment who are accepted to inpatient rehabilitation will increase. Further, because previous research indicates that CO-OP is associated with improvements in functional independence, activity performance, self-efficacy, and participation, including in those with demonstrated cognitive impairment [10–15, 22, 23], we expect to see similar positive patient outcomes. Aligning with the three expected project outputs outlined previously in the manuscript, three specific research questions are posed:Is the implementation of CO-OP KT associated with a change in the proportion of patients with cognitive impairment following a stroke accepted to inpatient rehabilitation?Is the implementation of CO-OP KT associated with a change in rehabilitation clinicians’ practice, knowledge and self-efficacy related to implementing the CO-OP approach, immediately following and 1 year later?Is CO-OP KT associated with changes in activity, participation, and self-efficacy to perform daily activities in patients with cognitive impairment following stroke at discharge from inpatient rehabilitation and at 1-, 3-, and 6-month follow-ups?

## Methods/Design

To answer the three questions, three interrelated studies will be conducted at five inpatient rehabilitation units in the Greater Toronto Area. See Fig. 2 for a visual depiction of all three studies and expected timeline. The first question, which relates to changes at the health system level, will be addressed using a quasi-experimental, interrupted time series design (Study 1); the second, which relates to changes in health-care professional knowledge, practice, and self-efficacy, will be addressed using a single group pre-post evaluation design (Study 2); and the third, which relates to patient outcomes, will be addressed using a non-randomized design with historical controls (Study 3). Table 2 provides an overview of outcomes, indicators, and their timing for all three studies.

**Fig. 2 Fig2:**
[figure not shown]
Toronto stroke networks knowledge translation (KT) infrastructure

### Study 1: admission to rehabilitation

An interrupted time series (ITS) design provides an estimate of the effect of an intervention using a long series of measurements of dependent variables, divided into pre-intervention and post-intervention segments [24]. It is useful when randomized designs are impossible or impractical, as is the case here.

Several years of retrospective rehabilitation referral and admission data are available through the TSNs. Monthly pre-intervention time points will collected for 28 months prior to the intervention implementation period, and post-intervention time points will be collected for 15 months thereafter. Thus, there will be 28 pre-intervention time points, called −T28 (intervention implementation minus 28 months), −T27, etc., to −T1. Following −T1, the CO-OP KT intervention will be implemented over a 3-month period. This 3-month intervention implementation period is called T0, during which, no data collection will occur. Next, 15 post-intervention monthly time points called T1, T2, etc., to T15 will occur. Aggregate electronic data will be collected at all pre- and post-intervention time points from the National Rehabilitation Reporting System (NRS) and the TSN’s E-Stroke rehab referral system. Data elements will include monthly summaries for the total number of rehabilitation referrals, number of rehabilitation admissions, number of referrals declined, reasons for declined referrals, age, sex, functional independence measure (FIM)™ [25] total, motor and cognitive scores of those admitted to rehabilitation, and discharge location.

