**Table 2 Tab2:** Outcomes, indicators, and timing for all studies

Outcomes	Indicators and description	Timing
Study 1: health system: data obtained from electronic referral system, health record, and NRS		
Access to inpatient rehabilitation	Monthly totals: # of inpatient rehab referrals, # of admissions, # declined; reasons for declined referrals	• −T28 to −T1 • T1 to T15
Inpatient rehab outcomes	Average monthly functional independence measure (FIM™) motor and cognitive scores (admission, discharge, and change)	• −T28 to −T1 • T1 to T15
	Monthly frequency of discharge locations (home, home with services, assisted living facility, or acute care)	
Study 2: health knowledge: data obtained from stroke rehabilitation team members and chart audits		
Rehabilitation team member practice change	Chart audits will be conducted 6 months (+/−1 month) before CO-OP KT implementation as a baseline and to confirm practice gaps previously identified with interviews [4], and repeated at 6 and 12 months (+/−1 month) following the CO-OP KT intervention. The chart audit review criteria will center around documentation of functional goals (e.g., independence with upper body dressing), rather than impairment-reduction goals (e.g., increase arm strength); evidence of patient involvement in the goal-setting process; evidence of teaching of cognitive and problem-solving strategies as an intervention technique; evidence of use of guided discovery as an intervention technique	• −T6 • T6, T12
Stroke rehab professional self-efficacy with knowledge and skills related to CO-OP	CO-OP essential elements self-efficacy tool: participants are asked to rate their ability to perform 25 elements on a 10-point scale, with 1 indicating that they cannot perform the element at all and 10 indicating that their performance is excellent. Face validity evaluated by five members of the International CO-OP Academy	• −T1 • T1 • T12

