### Recruitment and sample sizes

Five inpatient stroke rehabilitation units or combined stroke/neurology units in the TSNs have agreed to participate. Based on past experience, we estimate that the five units together will have approximately 80 admissions per month combined to contribute to the aggregate monthly data. For Study 1 (admission to rehabilitation), we will collect data from all patients aged 18 years or more who have completed inpatient rehabilitation with a primary diagnosis of stroke, defined as Rehabilitation Care Group (RCG) 01.1, 01.2, 01.3, 01.4 or 01.9. For Study 3, a subset of those patients will be recruited and the additional criteria of having at least some cognitive impairment will be applied, determined using the Montreal Cognitive Assessment© (MoCA©) [29]. The MoCA© is a 30-item test of cognitive impairment that includes elements of short-term memory recall; visuospatial capacity; aspects of executive functioning; attention, concentration, and working memory; language; and orientation. Patients with scores lower than 26 will be included. Additionally, patients will be required to have sufficient English language skills to complete the study assessments (see Table 1 for descriptions). Exclusion criteria are neurological diagnoses other than stroke, presence of major psychiatric illness or capacity issues requiring the use of a substitute decision maker under the Ontario substitute decision maker act. Based on data from a published acute rehabilitation CO-OP study [14], a sample size of 13 per group will have 80 % power to detect a between-group difference of 9 points on the FIM™, standard deviation of 8. Allowing for 30 % attrition from all sources, we will recruit 17 participants per group, 34 in total. Based on past projects, we expect a consent rate of one participant per site per month. Thus, recruitment is highly feasible, and will likely be completed in 4 months for each group.

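### As listed, the Study 1 data elements do not yield the Question 1 outcome: nothing is split by cognitive status, and the stated population conflicts with counting declined referrals

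*Protocol article*

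**What the plan says.** The research questions at the end of the protocol article's Background ask whether CO-OP KT is associated with a "change in the proportion of patients with cognitive impairment following a stroke accepted to inpatient rehabilitation". Methods/Design gives this question to Study 1, the interrupted time series.

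The section on Study 1 describes the data as follows:
- Level: "Aggregate electronic data will be collected at all pre- and post-intervention time points".
- Access: "Data elements will include monthly summaries for the total number of rehabilitation referrals, number of rehabilitation admissions, number of referrals declined, reasons for declined referrals".
- Cognition: FIM "total, motor and cognitive scores of those admitted to rehabilitation, and discharge location".

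Table 2 gives the access indicator as "Monthly totals: # of inpatient rehab referrals, # of admissions, # declined; reasons for declined referrals". It gives the FIM motor and cognitive indicators as monthly averages at admission, at discharge and for change.

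Recruitment and sample sizes defines the Study 1 population: "we will collect data from all patients aged 18 years or more who have completed inpatient rehabilitation with a primary diagnosis of stroke". The same section introduces the MoCA criterion (below 26) as an additional requirement for the Study 3 subset. Neither Data analysis nor Potential challenges and their solutions adds a split by cognitive status. The latter adds only an examination of each unit separately.

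**The concern.** Question 1 is about a subgroup, but the listed access series are not split by that subgroup. The question can be read in two ways, and each needs a count that is not listed:
- **Accepted share of impaired referrals.** This needs the number of impaired patients referred and the number of them accepted.
- **Impaired share of accepted patients.** This needs the number of admissions meeting a definition of impairment. A mean FIM cognitive score does not give that number, and no cut-off is stated.

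The rate that the listed totals do give directly is acceptance of all stroke referrals. It can rise or fall with no change in access for impaired patients, and it can stay flat while their access changes. Access for these patients is the problem that motivates the project, so the interpretation of the first research question is at stake.

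Separately, a population of patients who completed rehabilitation contains no declined referrals, although declines are a planned outcome.

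**Working it through.** The article states no sample size, power or effect size for Study 1, so there is no figure to reproduce. The check is whether the listed elements determine the outcome.

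**Inputs.** Admissions A = 80 a month over five units (Recruitment and sample sizes). Impaired patients are up to 30 % of stroke patients (Background). Monthly referrals R are not given. I assume overall acceptance of 60, 70 or 80 %, so R = 80/0.6 = 133, 80/0.7 = 114 or 80/0.8 = 100. The impaired share of referrals is not given either. I assume 20 to 40 %, which gives C impaired referrals.

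**1. Bounds on impaired acceptance from totals alone.** The lower bound is max(0, A − (R − C))/C and the upper bound is min(C, A)/C.

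| R | C at 20 % | Bounds | C at 30 % | Bounds | C at 40 % | Bounds |
|---|---|---|---|---|---|---|
| 133 | 27 | 0–100 % | 40 | 0–100 % | 53 | 0–100 % |
| 114 | 23 | 0–100 % | 34 | 0–100 % | 46 | 26–100 % |
| 100 | 20 | 0–100 % | 30 | 33–100 % | 40 | 50–100 % |

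The narrowest interval still spans half the scale. These bounds even take C as known, which the plan does not provide.

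**2. Same totals, different access.** Take R = 114, C = 34 and A = 80.
- 14 impaired patients admitted: impaired acceptance 14/34 = 41 %, other patients 66/80 = 82.5 %.
- 24 impaired patients admitted: impaired acceptance 24/34 = 71 %, other patients 56/80 = 70 %.

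Overall acceptance is 80/114 = 70.2 % in both cases.

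**3. Dilution.** With acceptance of other patients and case mix fixed, change in overall acceptance = impaired share × change in impaired acceptance. At a 30 % share, a 10-point rise moves the overall rate by 0.30 × 10 = 3 points. At 20 % it moves it by 2 points.

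**4. Case mix.** Fix acceptance at 50 % for impaired and 80 % for other patients, and let the impaired share of referrals rise from 30 to 40 %.
- Overall acceptance: 0.30 × 0.50 + 0.70 × 0.80 = 71 %, then 0.40 × 0.50 + 0.60 × 0.80 = 68 %.
- Impaired share of admissions: 0.15/0.71 = 21 %, then 0.20/0.68 = 29 %.
- Declines of impaired patients over all referrals: 0.30 × 0.50 = 15 %, then 0.40 × 0.50 = 20 %.

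All three move although access has not changed.

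**5. Averages.** A monthly mean FIM cognitive score can stay the same while the number of patients below a cut changes, because higher scores elsewhere offset it. The mean therefore does not give a proportion.

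**6. Population.** Everyone who completed rehabilitation was first accepted. Taken literally, acceptance in that population is 100 % by construction and the number declined is zero. The Study 1 section and Table 2 plan to count declines, so the statements conflict.

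**The case against.** The strongest reply is that this is a condensed article. Its list says what the data will include and does not claim to be complete. The referral system may hold cognitive status, and the full protocol may define the series. Reasons for declined referrals are listed and bear on cognition, as do admission FIM cognitive scores. The completers sentence stands beside the estimate of monthly admissions and may be meant only for the admitted-patient data.

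Much of this stands, and it rules out three stronger readings that a reader might infer:
- *Study 1 can never answer Question 1.* The document does not support this. The list is open, and the fields of the two source systems are not described.
- *Every declined referral is excluded.* The population sentence contradicts two explicit plans to count declines. It does not plainly override them.
- *The 3-point diluted effect would be lost in noise.* No referral volume or acceptance rate is given. The 26 to 33 % in the Background is a share of acute-care discharges, which is a different denominator. The relevant precision is that of a series of 28 months before and 15 after, not of one month.

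The reply does not supply the missing link. The list and Table 2 both omit the variable that the question turns on, while the list names age, sex and discharge location. Decline reasons are a partial proxy with no denominator of impaired referrals. A later analysis plan cannot recover a stratum from aggregates requested without it.

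**Conclusion.** The point holds as a statement about what is specified. The listed elements identify neither reading of Question 1, no definition of impairment is given for Study 1, and the population sentence contradicts the planned referral and decline counts.

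The size is best expressed as non-identification. Under the assumed referral volumes and impaired shares, the totals leave impaired acceptance anywhere within an interval at least 50 points wide, and in most scenarios within 0 to 100 %. The logical point does not depend on those assumptions. The dilution figure, about 3 points overall for a 10-point change, is secondary. It holds only if the share of up to 30 %, stated for stroke patients, also applies to referrals.

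**What to change.** Before the data request is made:

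1. State a definition of cognitive impairment for Study 1.
2. If E-Stroke holds cognitive status at referral, request monthly counts of referred, accepted and declined patients by that status. Make acceptance among impaired referrals the Question 1 series.
3. If it does not, request two proxies. From NRS, take the monthly count and proportion of admissions below a pre-set admission FIM cognitive cut, in place of the average. From E-Stroke, take cognition-related declines over all stroke referrals. Limit the Question 1 conclusion to these proxies and state that both move with referral case mix.
4. Reconcile the population sentence in Recruitment and sample sizes with the Study 1 section and Table 2, so that the access outcomes cover all adult stroke referrals to the five units. The FIM and discharge outcomes can keep an admitted-patient population.

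The cost is a changed request to two electronic systems already in use, plus wording, with no new data collection from patients. The article does not say whether decline reasons are usably coded, or whether FIM distributions can be retrieved for the 28 retrospective months. Both should be confirmed first. The proxy route has a further cost: it answers a narrower question than the one posed.
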